### Primary Outcomes

#### Child and Adolescent Trauma Screen

The Dutch version of the Child and Adolescent Trauma Screen 2 (CATS-2) [47,48] is a self-report and proxy-report measure for children (aged 7-18 years) and their caregivers. The questionnaire contains a list of potentially traumatic life events (16 items) and questions about PTSD symptoms (25 items; ie, re-experiencing, avoidance, emotional numbing, negative alterations in cognitions and mood, and hyperarousal). Respondents can answer each potentially traumatic life event with yes (scored as 1) or no (scored as 0). The questions about PTSD symptoms are rated on a 4-point Likert scale (range 0-3). A score of ≥2 indicates positive screening for PTSD symptoms. The highest possible total score is 60, with higher scores reflecting a higher severity of symptoms. The CATS-2 also asks informants to indicate whether the symptoms cause difficulties in daily life (yes or no). The CATS-2 has adequate psychometric properties [48].

#### The CAPS-CA-5

The CAPS-CA-5 [35,36,49] is used to determine the presence of PTSD based on the *DSM-5* criteria. In addition, with the CAPS-CA-5, we will collect information about the number of traumatic events and the type of experienced trauma. The CAPS-CA-5 is a 30-item structured clinical interview suitable for children aged 8-18 years. In addition, the CAPS-CA includes a Life Events Checklist consisting of 26 items related to stressful life events. The interviewer assesses per event if the adolescent has “experienced it,” “witnessed it,” “heard about it,” “is not sure about it,” or “never experienced it.”

Afterward, the interviewer assesses the frequency and intensity of PTSD symptoms experienced in the past month using a 5-point Likert scale (range 0-4). A score of ≥2 indicates the presence of a symptom. PTSD is present when an A criterion event has occurred, when symptoms are present for more than 1 month (criterion F), when the symptoms affect the adolescent’s daily life (criterion G), and when there is at least one symptom of re-experiencing (criterion B) and avoidance (criterion C) and 2 symptoms of emotional numbing, negative alterations in cognitions and mood (criterion D), and hyperarousal (criterion E). Subthreshold PTSD is present when the adolescent fully meets criteria A, F, and G and has at least one symptom of criteria B, C, D, and E, or has at least one of the B, C, D, or E symptom clusters. The highest possible total score is 80, with higher scores reflecting a greater severity of symptoms. The Dutch version of CAPS-CA-5 has adequate psychometric properties [35,49].

### Secondary Outcomes

#### Patient-Reported Outcomes Measurement Information System

The Patient-Reported Outcomes Measurement Information System (PROMIS) [50] is a questionnaire for children aged 8-17 years and will be used to measure anxiety (8 items), depression (8 items), and anger symptoms (9 items). The questions are rated on a 5-point Likert scale (range 0-4). The highest possible total score for anxiety and depression is 32 and 36 for anger, with higher scores reflecting a higher severity of symptoms. Raw scores will be converted to *t* scores. The PROMIS anger, anxiety, and depression scales displayed sufficient psychometric properties within the Dutch population [51,52].

#### The EQ-5D-Y-3L

The EQ-5D-Y-3L [53] assesses the perceived quality of life in children aged 8-15 years. This questionnaire maps the quality of life based on 5 dimensions: mobility, self-care, usual activities, pain, and anxiety or depression. Both self-report and caregiver proxy versions will be used. All 5 items of the EQ-5D-Y-3L are rated on a 3-point scale, indicating levels of difficulty as “no problems,” “some problems,” or “a lot of problems.” The highest possible total score is 15, with higher scores reflecting a higher severity of symptoms. The EQ-5D-Y-3L has adequate psychometric properties [54].

#### Risk-Behavior and Safety Questionnaire

We will assess risk behaviors by administering a self-report questionnaire based on previous work by Hendriks et al [25], who administered this questionnaire to children aged 12-18 years. This questionnaire assesses suicidal ideation, self-harm, and aggressive behavior with 8 items using an 11-point Likert scale, ranging from “no, not at all” (=0) to “yes, very much” (=10) [25]. Higher scores reflect a higher severity of symptoms. Alcohol use, drug use, inclination to medication, crisis contacts with mental health care professionals, and psychiatric hospitalization will be measured with 7 items on a dichotomous scale (yes or no). The psychometric properties of this instrument have not yet been examined.

#### PTSD Checklist for DSM-5

We will evaluate the presence and severity of the caregivers’ posttraumatic stress symptoms with the Dutch version of the PTSD Checklist for *DSM-5* (PCL-5) [55] The PCL-5 is a 20-item self-report questionnaire gauging the 4 cluster symptoms of PTSD. The caregiver indicates the degree of burden caused by each symptom on a 5-point Likert scale ranging from 0 (“not at all”) to 4 (“extremely”). The severity of symptoms can be determined either by adding the scores of the items within each of the four clusters or by summing all 20 items. The highest possible total score is 80, with higher scores reflecting a higher severity of symptoms. The PCL-5 has adequate psychometric properties [56].

#### Life Events Checklist for DSM-5

We will administer the Dutch version of the Life Events Checklist for *DSM-5* (LEC-5) [57] to assess the caregivers’ exposure to trauma. This is a self-report questionnaire that consists of 17 items related to stressful life events. The caregiver will specify their experience of each event by selecting from the options “happened to me,” “witnessed it,” “learned about it through an affected friend or family member,” “exposed through work,” or “unsure or not applicable.” The LEC-5 has adequate psychometric properties [58].

#### Outcome Rating Scale and Session Rating Scale

We will assess the adolescents' well-being after each BITT day through the Dutch version of the Child Outcome Rating Scale (ORS) [59]. Adolescents will mark their well-being on 4 visual analog scales that range from 0 to 10, providing information on their well-being (“How am I doing?”), well-being at home (“How are things at home?”), school (“How are things at school?”), and their overall sense of well-being (“How is everything going?”).

We will use the Child Session Rating Scale (SRS) [60] to assess how the child experienced the BITT sessions. Respondents will be asked to rate on a visual analog scale ranging from 0 to 10 the extent to which they felt that “they were listened to,” “what was done and talked about was important to them,” “they liked what was done,” and “hoped they would do something similar next time.”

Both the ORS and SRS have adequate psychometric properties in an adult population [61].

#### Demographics

We will collect demographic information by asking the adolescents and one of the caregivers at baseline about: age, gender, educational level, SES, ethnicity, residency (ie, urban and rural area), and previous and current psychological or psychiatric treatment (eg, psychotherapy, trauma therapy, and medication).

### Qualitative Secondary Study Parameters: Qualitative Interview About BITT Experiences

We will conduct interviews with adolescents, caregivers, and therapists about their experience with BITT in collaboration with 2 of our experts by experience (bachelor education level). Together with the 2 experts by experience, we will develop a broad topic list about experienced benefits and possible improvements of BITT. Topics will be related to adolescents’, caregivers’, and therapists’ preparation for and expectations of BITT, the effects of BITT, the added value of BITT compared to regular trauma therapy, and follow-up treatment. These interviews will be conducted individually with around 15 adolescents, caregivers, and therapists. In addition, we will hold focus groups with the therapists to collect their perspectives regarding BITT. We will conduct interviews 1 month after BITT. The 2 experts by experience will be closely involved in the preparation, conduction, assessment, and analyses of the qualitative interviews.

### Statistical Analysis

We will conduct the analyses in consultation with a statistical expert. Data analyses will include the following:

We will define the effects of BITT in terms of group differences between the BITT and WLCG. These differences will be tested according to both the intention-to-treat-principle and completers’ analyses. That is, the pre, post, and follow-up changes (BITT vs WLCG) on the continuous outcomes (ie, trauma symptoms, anxiety symptoms, depression symptoms, anger symptoms, quality of life, and self-harm) will be tested with mixed models; dichotomous outcomes (ie, suicide attempts and dropout) with generalized estimating equation (GEE).Mixed models will also be used to investigate possible moderation effects, which concern effects of (1) age, gender, SES, type of trauma, number of traumatic events, comorbidity, caregivers’ PTSD, and treatment center on PTSD; and (2) residency (ie, urban and rural) and ethnicity on BITT dropout.The qualitative interviews about the experiences of adolescents, caregivers, and therapists with regard to BITT will be verbatim transcribed and analyzed to conform to qualitative research standards.

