**Methods:**

This multicenter, single-blinded randomized controlled trial will be conducted in 4 youth care centers in the European and Caribbean Netherlands: Levvel, Karakter, Fornhese-GGz Centraal, and Mental Health Caribbean (Bonaire). We will randomize adolescents (12-18 years old) with PTSD to a BITT (n=50) or waitlist control group (WLCG; n=50). BITT comprises 1-week (ie, 5 consecutive workdays) intensive trauma treatment, encompassing daily 90-minute manualized sessions of trauma-focused cognitive behavioral therapy and eye movement desensitization and reprocessing. The day begins and ends with psychomotor therapy. Caregivers receive daily parental counseling sessions consisting of psychoeducation and social support skill training. We will conduct measurements at similar intervals for both groups: at baseline; directly after BITT or WLCG; and at 3, 6, and 9 months’ follow-up. The WLCG will receive BITT after the 3-month follow-up assessment. We will assess all study parameters using digital or face-to-face questionnaires and semistructured interviews. We will assess the primary outcome PTSD symptoms using the Child and Adolescent Trauma Screen 2 (CATS-2) and the Clinician-Administered PTSD Scale for *DSM-5* (*Diagnostic and Statistical Manual of Mental Disorders* [Fifth Edition])-Child/Adolescent Version (CAPS-CA-5).

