#### Secondary Objectives

The secondary objectives of the study are to investigate whether BITT for adolescents with PTSD:

in comparison to a WLCG, demonstrates effectiveness in reducing comorbid psychiatric symptoms (ie, anxiety, depression, and anger) and improving the quality of life;is safe (ie, does not increase suicide attempts or self-harm)reduces dropout rates;is affected by moderators (ie, age, gender, socioeconomic status [SES], type of trauma, number of traumatic events, comorbidity, caregivers PTSD, and treatment center) in its effect on PTSD symptoms and BITT dropout (moderators: residency [ie, urban and rural area] and ethnicity).

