### Study Design

In this multicenter, single-blinded RCT, we will examine the effectiveness of BITT compared to a WLCG. Participants will be recruited over 27 months (October 2022-December 2024). To determine the effectiveness of BITT, we will compare the outcomes of the BITT intervention group (n=50) with the outcomes of a WLCG (n=50). We will conduct assessments at similar time points for both groups: at baseline (T0), directly after BITT or WLCG (T1), and at 3 (T2), 6 (T3), and 9 (T4) months follow-up after the baseline measurement. The WLCG will receive BITT after the 3-month follow-up assessment. Figure 1 provides an overview of the study design.

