**Secondary**								
	Depression symptoms	PROMIS^m^ depression	A	A	A	A	A	A
	Anxiety symptoms	PROMIS anxiety	A	A	A	A	A	A
	Anger symptoms	PROMIS anger	A	A	A	A	A	A
	Quality of life	EQ-5D-Y-3L	A, C	A	A, C	A, C	A, C	A, C
	Risk-behavior and safety	Risk behavior and safety	A	—	A	A	A	A
	Parental PTSD	PCL-5^n^ including LEC-5^o^	C	—	C	C	C	C
	Rating of sessions and therapy	ORS^p^ and SRS^q^	—	A	—	—	—	—

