## Results

This project was funded in June 2021 and approved by the institutional review board in September 2022. As of September 2022, we enrolled 104 participants. Data will be collected until December 2025. Results are expected to be published in the summer of 2026.

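### The stated safety comparison by arm has no cut at T2, so waitlist events that follow the group's own BITT count as control events

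*Protocol article*

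**What the plan says.** Secondary Objectives asks whether BITT "is safe (ie, does not increase suicide attempts or self-harm".

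Statistical Analysis gives one rule for all effects: "We will define the effects of BITT in terms of group differences between the BITT and WLCG". It adds: "These differences will be tested according to both the intention-to-treat-principle and completers’ analyses". The same item lists self-harm among the continuous outcomes, tested by mixed models on changes over pre, post and follow-up, and suicide attempts among the dichotomous outcomes, tested by GEE. It names no last visit for the comparison and no analysis set defined by BITT received.

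Study Design says: "The WLCG will receive BITT after the 3-month follow-up assessment". Both arms continue to be assessed "and at 3 (T2), 6 (T3), and 9 (T4) months follow-up after the baseline measurement". In Table 2 the row "Risk-behavior and safety" is marked for the adolescent at T0, T1, T2, T3 and T4.

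Three other statements bear on the point. Study Design says that all care provided is registered in the research database. Ethics Approval says that serious adverse events are monitored until the study ends, and it times the risk-behaviour measurements from BITT rather than from baseline. Statistical Analysis introduces its list as what the analyses will include, which does not make the list exhaustive.

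**The concern.** Up to T2 the two arms differ in BITT by randomisation. After T2 both arms have been offered BITT, but the comparison still carries the labels BITT and WLCG. A suicide attempt or a rise in self-harm after a waitlisted adolescent's own BITT is then scored against the control arm.

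For safety the direction of this error matters. The objective is framed as the absence of an increase, so a null result reads as reassurance. If BITT does raise risk, scoring post-BITT waitlist events as control events moves the result towards null. If BITT lowers risk, the same rule hides the benefit.

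A second, lesser point follows. Cutting the comparison at T2 repairs it but leaves the waitlist courses outside any stated safety analysis, although the questionnaire continues after them.

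**Working it through.** The article prints no safety precision or event risk, so there is no figure of its own to reproduce. Its sample size (Power Analyses) concerns Cohen *d*=0.5, not safety.

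**Inputs from the article.** Arms of 50 and 50: "We will randomize adolescents (12-18 years old) with PTSD to a BITT (n=50) or waitlist control group (WLCG; n=50". BITT for the WLCG after month 3; last visit at month 9. Expected dropout about 25% (Power Analyses). The Results section reports 104 enrolled; with 52 per arm the full-uptake shares below do not change.

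**Assumptions.** BITT is given soon after T0 in the BITT arm and soon after T2 in the WLCG. Uptake in the WLCG is 100%, or 75% if the 25% dropout figure is borrowed for it. Visits follow the Study Design calendar.

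**1. Control-arm time that follows BITT.** 9 − 3 = 6 months of 9, or 67%.

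**2. What the waitlist courses contribute to post-BITT safety data.**

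| Measure | Full uptake | 75% uptake (37.5 courses) |
|---|---|---|
| Courses | 50/100 = 50% | 37.5/87.5 = 43% |
| Person-months | 6×50/(9×50 + 6×50) = 300/750 = 40% | 225/675 = 33% |
| Scheduled assessments (T1-T4 vs T3-T4) | 2×50/(4×50 + 2×50) = 100/300 = 33% | 75/275 = 27% |

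**3. Precision for a rare event.** With zero events in *n* courses, the one-sided 95% upper bound is 1 − 0.05^(1/*n*):
- *n* = 50: 5.8%
- *n* = 88 (75% uptake): 3.3%
- *n* = 100: 3.0%

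For an assumed true risk of 2% per course, the chance of seeing at least one case is 1 − 0.98^*n*: 64% for *n* = 50 and 87% for *n* = 100.

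**4. How far the arm comparison can be masked.** Assume, for illustration only, a risk of 2% per 3-month interval and 6% in the interval after BITT.
- BITT arm over 9 months: 1 − 0.94×0.98×0.98 = 9.7%
- WLCG over 9 months: 1 − 0.98×0.94×0.98 = 9.7%

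Pooled over all follow-up, the arms look identical although BITT triples the interval risk. Taken interval by interval, the same inputs give 6% against 2% up to T2, then 2% against 6% from T2 to T3. The full cancellation therefore belongs to a pooled comparison. A visit-wise one shows the excess early and then credits the later excess to control. The article does not say which of these the GEE will estimate.

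**5. Timing of visits.** Study Design counts months from baseline, whereas Ethics Approval counts them from BITT. On the first, the WLCG has two post-BITT assessments (T3, T4). On the second, it would have four, and its share of assessments would be 200/400 = 50%. The figures in step 2 depend on which statement holds.

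**The case against.** **The plan may already cover this.** A reader might infer that the waitlist courses are never analysed for safety and that their data are lost. The article does not support that. Its list of analyses is open, and a descriptive table by exposure is something an article may leave to a fuller document. Serious adverse events are followed to the end of the study and care is registered, so events can be linked to BITT. This stands, and the absence of such a table is not in itself an error. It does not remove the main point: for suicide attempts and self-harm the article does state the outcomes, models, comparison and analysis sets, and that stated rule runs past the crossover. Monitoring and registration govern collection and reporting, not the analysis.

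**About half of the safety information is at stake.** This is tempting because 50 of 100 courses are waitlist courses. It holds for courses at full uptake only. On the Study Design calendar the share is 40% of post-BITT person-time and 33% of assessments, and lower with incomplete uptake. The randomised evidence is not halved; it is intact up to T2.

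**An increase needs a control.** This is correct. After T2 the waitlist courses have no untreated concurrent group, so they add event rates and not evidence of an increase. The Introduction cites 48.8% self-harm and 20.1% suicide attempts at age 18 in adolescents with PTSD. These are not rates per interval, but they warn against reading post-BITT counts as caused by BITT. The zero-event bounds illustrate precision for a rare serious event and do not apply to self-harm analysed as a continuous score.

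**The data may not be ready for the fix.** This partly stands. The Risk-Behavior and Safety Questionnaire section lists suicidal ideation, self-harm, aggression, substance use, crisis contacts and hospitalisation, but not suicide attempts. Self-harm on 0-10 items has no stated threshold for worsening.

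**Conclusion.** The concern holds in a limited form. The only safety comparison stated is by randomised arm across follow-up with no cut at T2, so waitlist events after the group's own BITT count as control events for up to 6 of its 9 months. If BITT raises risk, this biases a conclusion of no increase towards reassurance. The extent depends on the model: cancellation can be complete in a pooled comparison, while a visit-wise one would show the effect at T1-T2 and reverse it later.

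The missing summary by exposure is secondary. At full uptake it would double the courses examined, from 50 to 100, and lower the zero-event bound from 5.8% to 3.0% (about 3.3% with 88 courses). These figures assume prompt BITT after T2 in the WLCG and zero events. The added courses are uncontrolled and can only support the randomised comparison.

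**What to change.** Amend Statistical Analysis as follows:

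- Limit the comparative safety analysis to T0-T2: T1 and T2, adjusted for T0.
- State that WLCG events after the start of its BITT are not control events.
- Add a supportive, non-randomised summary of all participants who start BITT in either arm, counted from their own BITT start, with T0 as reference in the BITT arm and T2 in the WLCG. Give exact 95% confidence intervals for event proportions. Show it overall and by original arm, because the first post-BITT questionnaire comes later in the WLCG (T3) than in the BITT arm (T1).
- Name the source for suicide attempts, such as the serious adverse event records, since the questionnaire as described does not list them.
- Report self-harm as change on its 0-10 items, or fix a threshold for worsening in advance.
- Reconcile Study Design (visits timed from baseline) with Ethics Approval (visits timed from BITT), so that each WLCG safety assessment can be dated relative to BITT.

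The cost is about one paragraph and one table, largely from data already being collected, with no new visits or participants. The source for suicide attempts has to be confirmed. The T0-T2 cut gives up no randomised contrast, because the arms no longer differ in access to BITT after T2.

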### Ethics Approval

This study will be conducted in accordance with the Declaration of Helsinki. The ethics review board of the Amsterdam University Medical Center in the Netherlands approved this study (2022.0347, September 12, 2022). We will handle participant data in compliance with the General Data Protection Regulation (GDPR). All adolescents will give written informed consent, and legal guardians of adolescents aged 12-15 years will also provide consent before conducting any study procedures. All serious adverse events will be monitored and reported to the Medical Ethical Committee of the Amsterdam University Medical Center until the end of the study. In addition, during the measurements (directly, 3, 6, and 9 months after the BITT) we assess PTSD symptoms, comorbid symptoms, and risk behavior. In case of safety concerns, we contact the referring professional of the adolescent. Participants will receive a voucher of 10 euros (US $11.36) upon completing the final measurement.

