## Discussion

### Anticipated Findings

This study protocol describes the design of a multicenter, single-blinded RCT with the aim of examining the effectiveness of BITT compared to a WLCG in treating PTSD among adolescents. We hypothesize that the results will demonstrate a superior effect of BITT compared to WLCG and we expect a change in PTSD and comorbid symptoms among adolescents in the BITT group, while symptoms in adolescents in the WLCG will remain unchanged. We hypothesize that BITT can be a suitable treatment option for traumatized adolescents who do not receive the available treatment options due to high treatment avoidance, those who do not experience sufficient symptom decrease after regular trauma treatment or adolescents who drop out of treatment. For this group of severely traumatized adolescents, BITT could potentially be effective. Research in the adult population already has shown positive effects of BITT on PTSD symptoms [21]. However, not much research has been conducted among children and adolescents. Pilot studies show that BITT can be a safe (ie, no increased risk of suicidality) and effective treatment for adolescents with PTSD [25,26,30,31] but RCTs into its effectiveness are lacking and urgently needed.

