In addition, in determining the effectiveness of the treatment program, we will use multiple sources of information which improve the reliability of the results [66]. We ask adolescents to report their symptoms over time, semistructured interviews are used which also incorporate clinical judgment, and caregivers are actively engaged as informants in monitoring treatment outcomes. In addition, we conduct measurements including a 3-, 6-, and 9-month follow-up, which enables us to detect an effect of BITT over time.

Despite these strengths, possible limitations need to be acknowledged. First, although an RCT design remains the golden standard in clinical research, it comes with challenges. RCTs often operate in controlled environments with strict eligibility criteria, which may limit the external validity or applicability to diverse populations. Furthermore, participants who volunteer for the study may differ systematically from those who do not, thus affecting the generalizability of the findings. However, by conducting the study across multiple (cross-cultural) sites, each with distinct teams serving diverse target populations, we aim to achieve a diverse and representative study sample, thereby minimizing the limitations to the fullest extent possible.

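### The BITT vs WLCG test is not limited to the visits before the waitlist arm receives BITT, so T3 and T4 are labelled as a contrast they do not measure

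*Protocol article*

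**What the plan says.** The Statistical Analysis section of the protocol article states: "We will define the effects of BITT in terms of group differences between the BITT and WLCG". The differences are "tested according to both the intention-to-treat-principle" and in a completers' analysis. What is tested is "the pre, post, and follow-up changes (BITT vs WLCG) on the continuous outcomes", using mixed models, with GEE for suicide attempts and dropout.

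Study Design sets the same visits for both arms: baseline (T0), directly after BITT or the waitlist week (T1), "and at 3 (T2), 6 (T3), and 9 (T4) months follow-up after the baseline measurement". The same section says: "The WLCG will receive BITT after the 3-month follow-up assessment". Table 2 schedules both primary instruments, CATS-2 and CAPS-CA-5, at every visit from T0 to T4.

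Three other statements bear on this:
- Anticipated Findings expects improvement under BITT, "while symptoms in adolescents in the WLCG will remain unchanged", without a time limit.
- The same part of the discussion says "we conduct measurements including a 3-, 6-, and 9-month follow-up, which enables us to detect an effect of BITT over time".
- Ethics Approval describes the assessments differently from Study Design: "during the measurements (directly, 3, 6, and 9 months after the BITT".

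The article does not confine the between-group test to T0-T2, name a primary time point, or give T3 and T4 a role of their own.

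**The concern.** The primary objective is to compare BITT with a waitlist control. That contrast exists only while the control arm is waiting, at T1 and T2. By T3 the plan has both arms offered BITT. Two of the three follow-ups therefore carry the BITT vs WLCG label although no waitlist arm remains.

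If BITT works, the WLCG should improve after T2, and the expectation of unchanged WLCG symptoms cannot hold at T3 and T4. An analysis that pools all visits can then go wrong in either direction. The catch-up can dilute a real effect, or a change in the WLCG after T2 can by itself produce a significant group-by-time result. Leaving the visits open also allows the contrast to be chosen once results are known.

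The clock matters for the same reason. Three, six and nine months after baseline and after BITT are different dates for the WLCG, whose T1 and T2 come before its BITT.

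**Working it through.** **The plan's own figure.** Power Analyses gives 66 evaluable participants (33 per arm) for at least 80% power at d=0.5, and 66/0.75 = 88 reproduces. The 66 can be neither confirmed nor called wrong, because alpha, correlation and the visits used are not stated. A plain two-sided 5% two-sample comparison needs 126. Baseline adjustment at one visit with correlation 0.69-0.70 gives 66, and the baseline-adjusted mean of T1 and T2 with correlation 0.5 gives 64. The power statement therefore does not show which visits the test was meant to use.

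**Inputs.** From the article: d=0.5 and 33 per arm. Assumed: two-sided alpha 0.05, compound symmetry with correlation ρ of 0.3, 0.5 or 0.7, baseline adjustment, and a true difference of 0.5 SD at T1 and T2. At T3 and T4 the WLCG is assumed to gain a share c of the BITT effect.

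**A. Equal-weight average over visits.** The baseline-adjusted variance of the mean of k post-baseline scores is v = (1+(k−1)ρ)/k − ρ². The noncentrality is d/√(2v/n), with a noncentral t.
- k=2: v = 0.56, 0.50, 0.36 for ρ = 0.3, 0.5, 0.7.
- k=4: v = 0.385, 0.375, 0.285.
- Average effect over T1-T4: (0.5+0.5+0+0)/4 = 0.25 for c=1, and (0.5+0.5+0.25+0.25)/4 = 0.375 for c=0.5.
- Example, ρ=0.5, n=33: 0.5/√(2×0.50/33) = 2.87 for T1-T2, and 0.25/√(2×0.375/33) = 1.66 for T1-T4 with c=1.

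| Power, 33 per arm | ρ=0.3 | ρ=0.5 | ρ=0.7 |
|---|---|---|---|
| T1-T2, d=0.5 | 76% | 81% | 92% |
| T1-T4, full catch-up | 36% | 37% | 47% |
| T1-T4, half catch-up | 68% | 69% | 80% |

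At 37 per arm (100×0.75 = 75 evaluable) and ρ=0.5, the fall with full catch-up is from 85% to 41%.

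**B. Joint group-by-time test, T0-T4.** Work with the four changes from T0, whose covariance is (1−ρ)(I+J), where J is the matrix of ones. The noncentrality is (n/2)·δ′[(1−ρ)(I+J)]⁻¹δ, referred to F with 4 and 2n−5 degrees of freedom. Take no difference at T1 or T2 and a 0.5 SD WLCG gain after T2, so δ = (0, 0, 0.5, 0.5) in absolute size. The quadratic form is (0.5 − 1/5)/(1−ρ) = 0.3/(1−ρ). At ρ=0.5 and n=33 the noncentrality is 16.5×0.6 = 9.9.

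| Rejection | ρ=0.3 | ρ=0.5 | ρ=0.7 |
|---|---|---|---|
| 33 per arm | 51% | 67% | 90% |
| 50 per arm | 73% | 87% | 99% |

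The reverse pattern, a 0.5 SD effect at T1 and T2 followed by full catch-up, gives the same 0.3/(1−ρ). The joint test cannot tell the two situations apart.

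**C. Linear slope of the group difference.** Place visits at 0, 0.25, 3, 6 and 9 months (T1 at 0.25 is assumed) and fit least squares. Over T0-T2 the slope is +0.098 SD per month in favour of BITT. Over T0-T4 it is +0.031 with no catch-up, −0.002 with half and −0.034 with full catch-up. The step from +0.098 to +0.031 reflects a straight line fitted to a plateau. Only the further fall, and the change of sign, comes from the WLCG receiving BITT.

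**The case against.** The strongest reply is that the article specifies none of models A to C. It says mixed models and changes, which fits categorical time with visit-specific contrasts, and under that model the T1 and T2 estimates are untouched. The crossover is openly disclosed, and exact contrasts are often left to an analysis plan. This stands against any claim that the randomised estimate is necessarily corrupted, which a reader might infer. It does not remove the point, because the article itself labels follow-up changes without limit as BITT vs WLCG.

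The illustrated harms also come from different models and do not add up. Under the joint test with a true T1/T2 effect and full catch-up (ρ=0.5, 33 per arm), including T3 and T4 raises rejection from 52% to 67%, although part of that comes from the catch-up. Full catch-up is an assumption. Both arms may also receive EMDR or TF-CBT outside BITT, so the trajectories are not simply on and off.

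Two further strong readings are tempting. One is that the discussion's sentence on 6- and 9-month follow-up is false. It does not claim that those visits are controlled, and durability within the BITT arm is a fair reading, so it needs qualifying only. The other is that T3 and T4 have no randomised value. As randomised, they still give a valid comparison of immediate with delayed BITT.

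The clock mismatch is real but editorial: it occurs in a safety-monitoring sentence.

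**Conclusion.** The concern holds as a defect in the stated contrast. Read literally, the plan tests T3 and T4 as BITT vs waitlist when both arms are due to have been treated. T1 and T2 remain sound if they are estimated visit by visit. A pooled, linear or joint analysis over T0-T4 would not answer the primary objective, and nothing in the text rules one out.

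The size cannot be given as one number. It ranges from no effect on the T1 and T2 estimates (categorical time, visit-specific contrasts) to a halved average effect with power of 36-47% (T1-T4 average, full catch-up). For a joint test there is a 51-90% chance at 33 per arm of rejecting with no T1/T2 difference at all. These figures rest on the assumed correlation, compound symmetry and catch-up, none of which the article gives.

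**What to change.** 1. **Statistical Analysis:** state that the confirmatory BITT vs WLCG test, for both the mixed models and the GEE, uses T0, T1 and T2 only.
2. **T3 and T4:** label them as a secondary comparison of immediate with delayed BITT, as within-arm maintenance, or both. For within-arm use, take the WLCG's T2 value as its pre-BITT value.
3. **Anticipated Findings:** limit the expectation of unchanged WLCG symptoms to the period up to T2, and say that the 6- and 9-month data are not a BITT vs waitlist comparison.
4. **Clock:** reconcile Ethics Approval (months after BITT) with Study Design (months after baseline), so that each visit has one definition per arm.

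The cost is wording only, with no new data or participants and no change to the visit schedule. It should be settled before the outcome data are analysed, so that the choice of visits cannot depend on the results.
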